#### 2.6.2. Continuous and categorical variables

Descriptive statistics including reported means ± standard deviation for continuous variables [questionnaires including MNSI-physical assessment, Neuropathy Total Symptom Score (NTSS), modified Medical Research Council Scale (mMRCS), Neuropathic Pain Symptom Inventory (NPSI), McGill Pain Questionnaire (MPQ), Pittsburgh Sleep Quality Index (PSQI), and International Physical Activity Questionnaire (IPAQ) summative scores, visual analog scale (VAS), anthropometrics, diabetes duration, hemoglobin A1c, and serum micronutrient levels] and proportions for categorical variables [number of adverse events, dietary adherence, insulin use, leprosy clinical status (according to the WHO and Ridley Jopling classification systems), frequency and prevalence of inflammatory leprosy reactions, corticosteroid use] will be reported by each study group (57). Between- and within-group comparisons will also be made for continuous variables using the Student’s *t*-test with reported *p*-values, and for categorical variables using the chi square or Fisher’s exact tests, reporting *p*-values with odds ratios and 95% confidence intervals. Statistics will also be reported for all time points including baseline, and end of study. Multivariate logistic regression adjusting for covariates [such as age, sex, PROGRESS+ factors (58, 59), level of physical activity, smoking status, alcohol consumption, comorbidities, diabetes status] and potential effect modifiers (such as change in weight over time, medication de-escalation over time) will be carried out to ascertain the impact of a WFPBD on PNP in leprosy patient sub-populations and under various conditions. All statistical analysis will be carried out using GraphPad Prism 8 (GraphPad, United States).

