### 2.2. Study objectives and hypothesis

The overall objective of this study is to demonstrate the effect of a dietary lifestyle intervention, specifically a WFPBD, on neuropathic pain variables in leprosy. It is hypothesized that patients may demonstrate a statistically significant improvement in sensory and motor neuropathy, as well as pain, on comprehensive questionnaires and objective QST and muscle testing both within and between groups at study end. Secondary objectives include contextualizing the significance of diet in the treatment of chronic leprosy sequelae by demonstrating high tolerability and a limited side effect profile alongside aforementioned improvements in neuropathic pain. It is hypothesized that a WFPBD has the potential to serve as a low-risk, low-cost, low-tech intervention for chronic neuropathic pain, improving function and reducing overall morbidity of leprosy.

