#### 2.5.2. Consent, randomization, and blinding

Patients with a history of leprosy will be pre-screened for inclusion via clinical records prior to routine follow up. Study personnel will approach eligible patients experiencing active or treated (“cured”) leprosy, as well as subjective neuropathic pain at participating tropical disease institutions. Eligible participants will receive a comprehensive in-person review of the trial protocol, including data collection requirements, and will be given the patient consent form. Patients will voluntarily confirm willingness to participate and will be free to withdraw at any point. Upon consent to enrolment, participants will be randomized to either the WFPBD intervention group, or standard of care control group. To ensure equal distribution and matching between study groups, randomization will be carried out using a stratified block method (52). Participants will be assigned to strata primarily by study site, followed by sex (male/female), and lastly age-band (18–65, >65) (Figure 2). Random sequence generation will be carried out using a computer-generated allocation sequence. Study investigators, physicians, and participants will not be blinded to group allocation due to the transparent nature of the dietary intervention and counseling. However, primary end points will be collected by independent study personnel, blinded to group allocation, allowing for a single-blinded protocol.

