## 3. Projected outcomes

### 3.1. Data collection

Outcomes will be collected at both baseline and at study end by dedicated personnel blinded to group allocation. Data will be housed on a password-protected and encrypted database generated on a secure drive which will be locked in the respective study centres. Prior to database entry, all patient and study data will be anonymized, and a master list linking patient identification and consecutive study numbers will be generated, secured, and housed separately to said database and to which only the study investigators will have access. Data collected for this study cannot be linked to a specific patient, and the principal investigator and study researchers will be the only individuals who have access to this information. Following final data collection, data will be pooled across study centres and analysis will be conducted within the research lab of the principal investigator.

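### The continuous primary scores are compared by an unadjusted t-test that uses baseline inefficiently at best and leaves out the stratification factors, and within-arm p-values carry inferential weight

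*Protocol article*

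**What the plan says.** - **Test (2.6.2).** "Between- and within-group comparisons will also be made for continuous variables using the" Student's t-test, with p-values. The continuous variables listed include the MNSI physical assessment, NTSS, mMRCS, NPSI, MPQ and VAS, all of which section 3.2 lists as primary. The section does not say whether final scores or changes are compared.
- **Baseline (3.1).** "Outcomes will be collected at both baseline and at study end by dedicated personnel blinded to group allocation". A baseline value therefore exists for every scale.
- **Randomisation (2.5.2).** "Participants will be assigned to strata primarily by study site, followed by sex (male/female), and lastly age-band (18–65, >65").
- **Adjusted model (2.6.2).** "Multivariate logistic regression adjusting for covariates [such as age, sex, PROGRESS+ factors" and others. Its purpose is "to ascertain the impact of a WFPBD on PNP in leprosy patient sub-populations and under various conditions". Age and sex are named; site and baseline score are not.
- **Hypothesis (2.2).** Significant improvement is expected "both within and between groups at study end".

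**The concern.** There are two separate problems.

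**Efficiency.** A baseline score and three stratification factors are collected on everyone, and the stated efficacy test adjusts for none of them. A two-sample t-test on final scores discards the baseline. On change scores it uses the baseline with a fixed coefficient of one, which is less efficient than estimating that coefficient. The logistic regression does not fill the gap: it needs a binary outcome, it is aimed at sub-populations, and it names neither site nor baseline score.

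**Interpretation.** A before-after p-value in one arm is not protected by randomisation. Participants have pain or neuropathy at entry and know their allocation. Both arms continue their leprosy treatment, and the diet arm also receives an hour of counselling each week. Natural course, concurrent therapy, attention and some regression to the mean can all move a largely self-reported score. Within-arm p-values printed beside the between-arm result, under a hypothesis that names both, may be read as evidence for the diet.

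**Working it through.** **Inputs.** From 2.6.1: MNSI questionnaire 5.3 ± 2.5 against 7.1 ± 2.8, 80% power, about 60 evaluable, 14% loss, about 70 randomised. Alpha is printed as 0.5; I use two-sided 0.05. The baseline-to-final correlation ρ, the share of variance explained by strata and any common improvement are not in the document, so each is an assumed range.

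**1. The plan's own figure.** n per arm = 2·SD²·(z₁₋α/₂ + z₀.₈)²/Δ², with Δ = 7.1 − 5.3 = 1.8.
- Two-sided 0.05, SD 2.5: 2 × 6.25 × 7.849/3.24 = 30.3, so 31 per arm, 62 in total.
- One-sided 0.05, SD 2.8: 29.9, so 30 per arm, 60 in total.
- Loss: 60/0.86 = 69.8, so 70.

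The plan's 60 and 70 are thus consistent with an unadjusted comparison of two final means. An alpha of 0.5 gives only 6 to 24 in total. The plan does not show which route it took.

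**2. Power with 30 evaluable per arm.** Pooled SD = √((2.5² + 2.8²)/2) = 2.654, so d = 1.8/2.654 = 0.678. The noncentrality for final scores is 1.8/(2.654·√(2/30)) = 2.63 on 58 df, which gives 73.3% power. For the alternatives, replace the SD:
- ANCOVA: SD·√(1 − ρ²)
- change score, with equal SD at both visits: SD·√(2(1 − ρ))

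| ρ (assumed) | t-test, final | t-test, change | ANCOVA |
|---|---|---|---|
| 0.2 | 73% | 53% | 75% |
| 0.3 | 73% | 59% | 77% |
| 0.4 | 73% | 65% | 80% |
| 0.5 | 73% | 73% | 85% |
| 0.7 | 73% | 92% | 95% |

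ANCOVA is ahead of both throughout. Its variance factor (1 − ρ)(1 + ρ) is below 1 for any ρ other than 0, and below 2(1 − ρ) for any ρ below 1.

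**3. Strata left out.** I simulated no treatment effect, N = 60 and balanced allocation within 8 strata (two sites × sex × age band; the number of sites is an assumption). If strata explain 10%, 20% or 30% of outcome variance, the true size of the nominal 5% t-test is about 4.0–4.4%, 2.8–3.1% and a little over 2%. The exact values shift slightly with the simulation set-up. At 5% of variance the size is close to nominal. The direction is always conservative.

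**4. Within-arm test with no diet effect.** Take a paired t-test with n = 30, 29 df and noncentrality δ√30, where δ is a common improvement in SDs of change.

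| δ (assumed) | Noncentrality | P(diet arm significant) |
|---|---|---|
| 0.2 | 1.10 | 18.5% |
| 0.3 | 1.64 | 36% |
| 0.5 | 2.74 | 75% |

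At ρ = 0.5 the SD of change is 2.654, so these are shifts of about 0.5, 0.8 and 1.3 MNSI points. At ρ = 0.5 and a 1.0-point shift in both arms, the chance is 51% in each arm. The diet arm alone is then significant with probability 0.514 × 0.486 = 25%.

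**The case against.** **The t-test may be on change scores.** It may, so a reader who infers that baseline is ignored altogether goes beyond the text. What stands is that a change-score t-test never beats ANCOVA and is worse than the final-score test when ρ is below 0.5.

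**Age and sex are in the regression list, and the list is open-ended.** True, so two of the three stratifiers do appear in the plan. But that model does not adjust the efficacy comparison, and logistic regression does not suit a continuous score.

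**An unadjusted t-test is valid in a randomised trial.** Correct. A reader might infer that ignoring the strata raises the false-positive rate. It does the opposite, so this part concerns efficiency only.

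**The hypothesis says within and between.** Read literally, a null between-arm result fails it. The stronger reading, that within-arm significance alone would count as success, is not in the document. The 18.5% to 75% above is the chance that one paired test is significant, not the trial's false-claim rate. Regression to the mean is also weaker than usual because 2.3 admits any degree of neuropathic pain with no minimum score, and outcomes are collected by blinded staff. Participants are nevertheless unblinded, and natural course, therapy and attention remain.

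**An unseen SAP may settle this.** It could add detail, but it would have to replace a test and a hypothesis that the article already states.

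**Conclusion.** The point holds as a matter of efficiency and interpretation; it does not make the between-arm test invalid. With the plan's own effect, 30 evaluable per arm and two-sided 0.05, ANCOVA gains between 2 and 22 percentage points over a final-score t-test (75% to 95% against 73%) for ρ of 0.2 to 0.7. A reader should not infer that adjustment always restores the planned 80%: it does so only if ρ is about 0.4 or more, and the document gives no value. The loss from omitting the strata depends on an assumed share of variance and is conservative. The within-arm p-values are the more serious part, because they can be significant with no diet effect at all and the hypothesis names them. How often depends on the assumed common improvement.

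**What to change.** In 2.6.2, make the between-arm difference at study end the sole efficacy test for each continuous primary scale. Estimate it by a linear model (ANCOVA) with treatment, baseline score, site, sex and age as main effects, and report the adjusted difference with its 95% CI. Main effects suffice; with about 70 patients, a term for every stratum combination is not needed. Check the model's fit for bounded scales, in particular the mMRCS with its ceiling of 5. Report within-arm changes as means with confidence intervals and no p-values, and delete the within-group element from the hypothesis in 2.2.

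The cost is a few sentences in 2.6.2 and 2.2. No extra data, visits or patients are needed.

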#### 2.4.2. Lifestyle counseling

Participants in the intervention group will be instructed to follow a WFPBD for 24 weeks. The study duration was chosen as a conservative estimate of comparable lifestyle-based interventional trials that demonstrated statistically significant improvements in diabetes-related neuropathy outcomes (18, 19). The diet will emphasize vegetables, fruits, whole-grains, nuts, and legumes, while omitting animal products, and limiting fat intake (Table 2). Selection of specific plant-based components may differ across study sites in concordance with local culinary preferences and cultural practices related to food. By tailoring the diet to the unique cultural diaspora affected by leprosy, many of which already endorse plant-based components, we seek to enhance adherence and acceptability to the diet overall. Likewise, current economic projections suggest that diets seeking to reduce animal products are more affordable than current standard diets across all socioeconomic levels – particularly due to inclusion of global staples such as tubers, beans, legumes, and rice – further enhancing accessibility (48–50). Participants will receive weekly support and guidance via 1 h counseling sessions with registered dieticians or the equivalent at each participating site. Sessions will be designed to disseminate comprehensive guidelines for following the WFPBD including culturally acceptable recipes and addressing concerns or knowledge gaps regarding the intervention. Participants in both the intervention group, and control group will be instructed to continue their respective leprosy therapeutics as prescribed throughout the duration of the study. Finally, dietary adherence will be measured via monthly random 24 h dietary recalls, and participants are free to withdraw at any point during the trial if they no longer wish to participate.

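### Section 2.6.2 applies chi-square or Fisher's exact tests to within-group (before-after) categorical comparisons, which treats paired data as independent; the p-values and odds-ratio intervals are then invalid, usually conservative

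*Protocol article*

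**What the plan says.** In the protocol article, Section 2.6.2 (Continuous and categorical variables), one sentence sets out the tests. Its subject is "Between- and within-group comparisons will also be made". It assigns Student's t-test to continuous variables, and continues "and for categorical variables using the chi square or Fisher’s exact tests", reporting p-values "with odds ratios and 95% confidence intervals". The next sentence adds: "Statistics will also be reported for all time points including baseline, and end of study".

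The categorical variables listed in the same section are adverse events, dietary adherence, insulin use, leprosy clinical status (WHO and Ridley-Jopling), frequency and prevalence of leprosy reactions, and corticosteroid use.

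Section 3.1 states the timing: "Outcomes will be collected at both baseline and at study end by dedicated personnel blinded to group allocation". Section 2.4.2 puts the diet period at 24 weeks. No McNemar test or other paired categorical method is named anywhere in the article.

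**The concern.** The categorical clause shares the sentence's subject, so chi-square and Fisher's exact tests apply to within-group as well as between-group comparisons. With only two time points, a within-group comparison can only set baseline against study end in the same participants. Chi-square and Fisher's tests of two proportions require two independent samples. Used here, they count 30 people as 60 and ignore the correlation between a person's two values.

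The name Student's t-test covers a paired form, so the continuous half of the sentence can be read charitably. Chi-square or Fisher with an odds ratio has no such natural reading. Because the article states the test, its scope and the effect measure, this is a method fixed badly and not a detail left to an analysis plan.

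At stake are the within-arm p-values and intervals for the four variables that can have a baseline and an end status: insulin use, corticosteroid use, prevalence of reactions and clinical status. A real change in status could be reported as non-significant with an interval that is too wide.

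**Working it through.** The article gives no figure for these comparisons, so there is none to reproduce. The check asks what the named tests do to paired data at this trial's size.

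**Inputs**
- Completers per arm: Section 2.6.1 gives 35 per group and 14% loss; 35 × 0.86 = 30.1, so 30.
- Level: two-sided 0.05 (assumed).
- Prevalence and switching: not in the article, so assumed and varied.

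**Formulas.** Let p10 be the proportion who stop, p01 the proportion who start, and p0 and p1 the baseline and end prevalence.
- Variance of the change if treated as independent: [p0(1−p0) + p1(1−p1)]/n
- Correct paired variance: [p10 + p01 − (p10 − p01)²]/n
- Exact McNemar: two-sided binomial test of stoppers against starters with probability 0.5. The mid-p version subtracts the probability of the observed split.

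**Standard errors, 50% to 25%, n = 30**
- As independent: √[(0.25 + 0.1875)/30] = 0.121, whatever the switching.
- Paired, nobody starts (p10 = 0.25, p01 = 0): √[(0.25 − 0.0625)/30] = 0.079.
- Paired, 10% of non-users start (p10 = 0.30, p01 = 0.05): √[(0.35 − 0.0625)/30] = 0.098.
- Paired, 20% of non-users start (p10 = 0.35, p01 = 0.10): √[(0.45 − 0.0625)/30] = 0.114.

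The independent-samples error is too large in each case, and the gap closes as starters increase.

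**Rejection rates, by exact enumeration over all outcomes with 30 pairs**

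| Scenario | Chi-square | McNemar exact | McNemar mid-p |
|---|---|---|---|
| No change, 50%; 20% of users stop, 20% of non-users start | 0.25% | 1.3% | 3.1% |
| 50% to 25%, nobody starts | 51% | 80% | 90% |
| 50% to 25%, 10% of non-users start | 52% | 57% | 67% |
| 50% to 25%, 20% of non-users start | 52% | 45% | 54% |
| 40% to 20%, nobody starts | 32% | 57% | 74% |
| 40% to 20%, 10% of non-users start | 37% | 38% | 49% |

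With no change and 15% or 25% switching in place of 20%, chi-square rejects in 0.06% and 0.6% of trials.

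**One data set (invented counts): use falls from 12/30 to 6/30.** Chi-square gives p = 0.091 and Fisher p = 0.158. The marginal odds ratio is (6/24)/(12/18) = 0.375, with unpaired 95% CI 0.12 to 1.19. These results are the same however the fall came about. McNemar's are not:

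| Stop / start | Exact p | Mid-p |
|---|---|---|
| 6 / 0 | 0.031 | 0.016 |
| 7 / 1 | 0.070 | 0.039 |
| 8 / 2 | 0.109 | 0.065 |
| 9 / 3 | 0.146 | 0.092 |

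The odds ratio of 0.375 is a marginal one. The matched odds ratio uses only the switchers (for example 1/7 = 0.14 with 7 stopping and 1 starting) and answers a different question.

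**The case against.** The strongest case on the other side concerns importance. Four parts of it stand.

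- **The size depends on starters.** The large power gaps assume that nobody starts treatment. One starter in the 12-to-6 example takes exact McNemar above 0.05; with two starters its p-value exceeds the chi-square one. Part of this is the exact test's own conservatism: mid-p keeps an advantage at 10% starting, and little at 20%. Section 1 says up to 65% of patients need corticosteroids after reactions, which can arise before, during and after therapy, so an assumption of no steroid starters is hard to defend.
- **The error is conservative.** With positive within-person correlation it costs power and does not create false positives. Only negative correlation would reverse this.
- **The variables are supportive.** The within-group hypothesis in Section 2.2 concerns neuropathy and pain, measured by scores that Section 2.6.2 treats as continuous.
- **Insulin data may be sparse.** Section 3.3.1 assesses insulin status in participants with steroid-related biochemical diabetes, a subset that may be well under 30 per arm. Power there would be low with any test.

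A reader might go further and infer that the planned tests would hide a steroid-sparing effect that the protocol expects. The article does not support that. The Abstract and Section 1 expect fewer adverse events related to corticosteroid treatment and better control of steroid-induced hyperglycaemia, and they cite lower insulin requirements in diabetes cohorts. They do not predict less steroid use. A reader might also infer that the odds ratios themselves are wrong. The unpaired ratio is a usable marginal point estimate; its interval and p-value are what fail.

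None of this makes an independent-samples test right for before-after data.

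**Conclusion.** The point holds in limited form. As written, Section 2.6.2 assigns independent-samples tests to paired categorical data. The within-group p-values and the intervals around the marginal odds ratio are invalid for the variables recorded at both time points, and they are conservative when status is positively correlated within a person.

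The consequence ranges from a substantial loss of power (51% against 80% to 90%) to almost none (37% against 38% for the exact test, 49% for mid-p). Where it falls depends on switching rates that the article does not give. The figures rest on 30 completers per arm, a two-sided 5% level and assumed prevalences.

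Between-arm chi-square and Fisher tests remain valid. Adverse events and adherence to the assigned diet have no baseline counterpart, and the continuous primary scores are not involved. The article gives no ground for reading this as a threat to the primary results or a source of false efficacy claims. It is a clear error in supportive analyses that should be corrected.

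**What to change.** Amend the sentence in Section 2.6.2:

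- Restrict chi-square and Fisher's exact tests, with their odds ratios and intervals, to between-arm comparisons.
- For binary before-after status within an arm, report the numbers stopping and starting, the paired difference in proportions with a 95% CI, and a McNemar test (mid-p, or exact), labelled descriptive. Name the version in advance, since the two can disagree at this size.
- For clinical status with more than two categories, use a marginal-homogeneity test (Stuart-Maxwell or Bowker) or a transition table from baseline to end category.
- State the denominator for insulin use, given the subset described in Section 3.3.1.

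The cost is one or two sentences. No new data are needed: both values are already planned for each participant, and McNemar's test needs only the two switching counts and the binomial distribution.

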### 3.2. Primary outcomes

#### 3.2.1. Michigan neuropathy screening instrument

The MNSI is a robust assessment of neuropathy identifiers that includes both a subjective questionnaire and objective measurements of perception via QST. Specifically, Semmes-Weinstein monofilaments will be used to measure sensation at the ulnar nerve-innervated dorsum of the hand bilaterally, given this site’s predilection for leprosy associated nerve damage, while a 128 Hz tuning fork will be utilized to test for vibration perception thresholds at the great toe (43, 60). This screening instrument has been widely used and validated in both diabetes and leprosy related neuropathy cohorts (19, 60). Scoring is based on a binomial yes/no response to specific questions where yes = 1 point and no = 0 points. Additionally, any abnormal QST result = 1 point, and a score of 4 or greater indicates the presence of neuropathy (60). The MNSI will be conducted at both baseline and at study end and will be utilized as one of the measurements for sensory neuropathy (Figure 3).

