### 3.4. Potential stratifiers/confounders

Beyond primary and secondary endpoints, potentially confounding variables will be collected and utilized for downstream data analysis including: (1) demographic data: age, sex, socioeconomic status [relative within country and absolute according to World Bank definitions (75)], occupation (considering level of manual work, repetitive tasks, and prolonged standing/walking/climbing), household membership (living alone vs. with family members), and education level; and (2) lifestyle-related information: level of physical activity (via the international physical activity questionnaire), tobacco and cannabis smoking and alcohol consumption habits (amount consumed/day), and environment (urban vs. rural; meters a.s.l.). Effect modifiers including weight loss over time and de-escalation of medication over time will also be considered. Considerations of intervention cost, feasibility, cultural acceptability, and adherence will also be collected and summarized in a thematic analysis (Figure 3).

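### The only covariate-adjusted efficacy model is logistic, although the pain and neuropathy scores are treated as continuous and no binary pain response is defined

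*Protocol article*

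**What the plan says.** Section 2.6.2 of the protocol article groups the efficacy measures under "continuous variables [questionnaires including MNSI-physical assessment, Neuropathy Total Symptom Score (NTSS), modified Medical Research Council Scale (mMRCS), Neuropathic Pain Symptom Inventory (NPSI" and so on, through the McGill questionnaire and the visual analog scale. These are summarised as mean ± SD and compared by Student's t-test. The other group is "proportions for categorical variables [number of adverse events, dietary adherence, insulin use, leprosy clinical status", followed by reactions and corticosteroid use; it contains no pain or neuropathy outcome. Section 2.6.1 sizes the trial on the mean MNSI questionnaire score.

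One adjusted model is named: "Multivariate logistic regression adjusting for covariates [such as age, sex, PROGRESS+ factors", then physical activity, smoking, alcohol, comorbidities and diabetes status, with "potential effect modifiers (such as change in weight over time, medication de-escalation over time" added. Its purpose is efficacy: it "will be carried out to ascertain the impact of a WFPBD on PNP in leprosy patient sub-populations and under various conditions". Section 3.4 adds that "potentially confounding variables will be collected and utilized for downstream data analysis", and lists socioeconomic status, occupation, "household membership (living alone vs. with family members), and education level", smoking, alcohol and environment.

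Cut-points appear only as diagnostic thresholds. For the MNSI, section 3.2.1 says "a score of 4 or greater indicates the presence of neuropathy"; section 3.2.3 reads an mMRCS score below 5 as reduced motor function. Neither is tied to the logistic model, and the pain scales (NPSI, MPQ, VAS) have no threshold.

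**The concern.** Logistic regression needs a categorical response. Followed literally, the plan obliges the analyst to cut a continuous score at a point that is not stated and could be chosen after seeing the data. Three things are at stake:

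- information in the score is discarded;
- the adjusted result is an odds ratio, which cannot be set beside the difference in means from the t-test;
- a long covariate list on about 60 participants leaves few events per parameter, a setting in which estimated odds ratios tend to lie too far from 1.

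This is the only adjusted efficacy estimate in the article and its stated route to conclusions about sub-populations. Section 3.3.1 gives particular weight to diabetes status and steroid use.

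**Working it through.** **Inputs.** Section 2.6.1 gives MNSI questionnaire 5.3 ± 2.5 (intervention) and 7.1 ± 2.8 (control), 80% power, about 60 evaluable, 14% loss and about 70 enrolled. The printed alpha of 0.5 is read here as two-sided 0.05, because only a value near that gives 60. Scores are assumed normal.

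**1. The plan's own figure.** Per arm, n = 2(1.96 + 0.842)² × SD²/difference². With SD 2.5 this is 2 × 7.849 × 6.25/3.24 = 30.3, an unrounded total of 60.6. Then 60/0.86 = 69.8, or 70 enrolled. The stated size is reproduced, and it rests on a continuous endpoint.

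**2. Power on the continuous score, 30 per arm.** Pooled SD = √[(6.25 + 7.84)/2] = 2.65, so d = 1.8/2.65 = 0.68. The normal approximation gives Φ(0.678√15 − 1.96) = Φ(0.67) = 75%; the t distribution gives about 73%.

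**3. Power after dichotomising, 30 per arm.** Power = Φ{[|p₂ − p₁|√n − 1.96√(2p̄q̄)]/√(p₁q₁ + p₂q₂)}, where q = 1 − p.

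- MNSI of 4 or more, taken as 3.5 on the normal scale because the score is a count: p₁ = 0.764, p₂ = 0.901, p̄ = 0.8325. The numerator is 0.748 − 1.035 = −0.287 and the denominator 0.519, so power = Φ(−0.55) = 29%. Cutting at exactly 4.0 gives 0.698 v 0.866 and 35% by this formula; the Wald test from a simulated logistic fit gives about 29%. About 30% is a fair summary.
- Near-median cut at 6.2: 0.359 v 0.626, power 54%. Simulated logistic regression split at the sample median gives about 60%.

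**4. Number of terms.** Eight named covariate entries, two effect modifiers and treatment make 8 + 2 + 1 = 11. If the single PROGRESS+ entry is replaced by five items from section 3.4 (socioeconomic status, occupation, household, education, environment), the count is 11 − 1 + 5 = 15, or 17 with a treatment interaction for each effect modifier. That expansion is an assumption.

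**5. Events per parameter, 60 evaluable.** A median split gives at most 30 events in the smaller class: 30/11 = 2.7, or 30/17 = 1.8. At MNSI of 4 or more (cut at 3.5) the smaller class is 30 × 0.236 + 30 × 0.099 = 10.1: 10.1/11 = 0.9, or 10.1/17 = 0.6.

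**6. Effect of the covariate load.** Simulated trials of 30 per arm with covariates unrelated to outcome, at least 1,500 per scenario:

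| | No covariates | 12 to 14 covariates |
|---|---|---|
| Median odds ratio, median split | about 3.0 | about 4.3–4.5 |
| Failed fits, median split | none | negligible |
| Failed fits at MNSI 4.0, planned effect | about 1% | about 4–9% |

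With the cut at 3.5, failed fits reach about 14% at 12 covariates. Because the covariates carry no information, the rise in the odds ratio is small-sample bias. At 12 covariates and a median split, power is about 52–53% for logistic and 63–65% for linear regression.

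**7. Type I error.** With 30 per arm and a forced 30/30 split, the Wald test with no covariates rejects at 19 v 11 or more extreme, an exact rate of 0.070. At 12 covariates the rate is 0.069 to 0.075, so almost none of the excess over 5% comes from covariates. With a fixed cut at 6.2 it went from 0.045 with none to 0.075 with 12. A covariate-driven rise is therefore between nothing and about three percentage points at that number.

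**The case against.** The strongest reply is that this is a supporting analysis. The randomised comparison is a t-test on continuous scores, the sample size rests on it, and neither depends on the logistic model. That stands. A reader might infer that the trial's main efficacy result is underpowered or biased by the model choice; the article does not support this.

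It can also be said that the covariate list is illustrative, that section 3.4 promises to use its variables without entering them all in one model, and that final selection belongs in an analysis plan not shown here. This stands for the count: 15 to 17 terms is a reading, not a stated number. It does not rescue the model, since the named entries alone leave fewer than 3 events per parameter at the most favourable cut.

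A later plan could also adopt the MNSI or mMRCS threshold. That would supply an endpoint but not recover the information: the MNSI threshold is the worse of the two cuts examined, and the pain scales have no threshold to adopt.

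A reader might further infer markedly inflated false-positive rates and frequent non-convergence. With 20 covariates a simulation gives a median odds ratio of 6.7, about 6% failed fits and about 9% type I error, but 20 terms go beyond what the article implies. Most of the 7% error at 12 covariates under a median split is present with none.

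Finally, many covariates also cost the linear model power, and a linear model suits the short mMRCS scale poorly. Both points are fair and shape the fix.

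**Conclusion.** The concern holds for the adjusted and sub-population analysis only. The named model does not match outcomes that the protocol itself treats as continuous, and no binary pain response is defined for it. Dichotomising lowers unadjusted power at 30 per arm from about 73% to about 60% or about 30%, depending on the cut. The covariate list, at its minimum reading of 11 terms, exceeds what about 60 participants can support in a logistic model, and 12 to 14 uninformative covariates push the median odds ratio from about 3.0 to about 4.3–4.5. Any covariate-driven rise in type I error is small at that number, and failed fits matter only at an unbalanced cut such as MNSI of 4 or more.

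These sizes assume normal scores with the means and SDs of section 2.6.1, alpha of 0.05, and covariates unrelated to outcome. The median split and the expansion of PROGRESS+ are also assumptions. The mismatch between model and outcome depends on none of them.

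**What to change.** In section 2.6.2, replace the logistic model for the continuous scores with linear regression (ANCOVA) of the end-of-study score on treatment, baseline score, the stratification factors of section 2.5.2 (site, sex, age-band) and at most one or two pre-named baseline factors, such as diabetes status. Examine sub-populations through a treatment-by-factor interaction for a few pre-named baseline factors, labelled exploratory. Keep logistic regression for outcomes that are truly binary, and use an ordinal model for the mMRCS if it is analysed on its 0–5 scale.

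This needs no new data, no additional participants and no change in trial conduct. The cost is a shorter covariate list: the remaining section 3.4 variables would be described rather than all entered in the model.
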